### Objectives {7}

Our objectives are to test a behavioural economics-informed SMS reminder message and a pre-recorded voice message that will be sent to the parents/guardians of school children who have been identified as having a visual impairment and referred to clinic. We hypothesise that these messages will be associated with a higher attendance rate than the current standard SMS reminder that is sent to all referred patients’ parents/guardians.

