### Trial design {8}

This is an automated, adaptive, parallel, four-arm, embedded, pragmatic RCT. We will start by testing the two SMS reminder messages head-to-head with an initial 1:1 allocation ratio, and then introduce the voice messages after a period of six weeks. We will use a Bayesian adaptive trial algorithm to perform adaptive allocation as the trial progresses.

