**Fig. 1 Fig1:**
[figure not shown]
First draft SMS reminder. Note: ‘Tebogo’ and ‘[name] are not real names

We will use four arms as outlined below. Each SMS will be sent two times; on the day of referral and on the day before the appointment.

Initially, we will only test arms 1 and 2 (the control and intervention SMS messages). We plan to introduce the voice message arms after 6 weeks. This is because we are interested in introducing new arms at later stages in the screening programme and want to observe how the allocation algorithm handles the introduction of new arms part-way through testing established interventions.Arm 1 (Control): Standard SMS reminder messages.Arm 2: New SMS reminder messages.Arm 3: Standard SMS reminder messages plus the pre-recorded voice reminderArm 4: New SMS reminder messages plus the pre-recorded voice reminder

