### Sample size {14}

Approximately 1000 children will be screened every day. Based on previous programmes, we expect approximately 160 of these children to be identified as requiring referral for further assessment and treatment. All of these children’s parents/guardians would receive the standard SMS reminders in a standard programme.

The adaptive allocation method that we are using does not use a pre-specified a sample size. Instead, the study will run until one of two criteria is met:There is a >95% probability that one arm is best.There is a >95% probability that the difference between the arms remaining in the study is <1%.

Depending on the effect of the interventions, one of the stopping criteria might be met after a few days; however, it could also take years before reaching a definitive conclusion. We will set a 3-month limit for this current study due to resource constraints.

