### Assignment of interventions: allocation

#### Sequence generation, concealment and implementation {16a, 16b, 16c}

Participants will initially be randomly allocated into two arms using computer-generated blocks of 12. As allocation and intervention delivery (sending SMS messages) is fully automated, there is no need for any of the human investigators to know participant allocation status. Once the first participants attend refractive services, the algorithm will begin adjusting the allocation ratio to favour the best-performing arms. There is no need for the investigators to see allocation status at this stage either. The data safety monitoring committee will be fully unmasked to allocation status and all outcome data and will have the power to stop the trial or suspend any arm.

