### Statistical methods

#### Statistical methods for primary and secondary outcomes {20a}

This study will use Thompson sampling a Bayesian approach to identify the best arm. This is a Bayesian algorithm widely used to learn about arms and optimise decision making [27] Every 24 h, the probability of each arm being the best arm overall will be estimated, using Monte-Carlo simulations to get the posterior probability estimates. As there is no evidence available on how the messages would perform relative to another, a regularising prior of Beta(100,000) (i.e. centred at *p*=0.5 with a 90% credible interval of 0.44–0.56) will be used to avoid overfitting extreme data in the early phase of the trial. It is expected that about 1,000 children will enrol every day, and the observed data will begin to dominate the prior within the first couple of days. Each arm will have a probability of being best between 0 and 100%, and the sum of all two probabilities will equal 100%. These probabilities will be compared to the stopping rules as to whether the trial should stop or continue into the next day. If the trial is to continue, the proportion allocated to each arm for the next day will be updated to be proportional to the estimated probabilities. We will conduct all analyses using the runif and rbeta functions in R (R Foundation for Statistical Computing, Vienna, Austria). Figure 2 illustrates participant flow and operation of the algorithm.

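### The allocation rule sets no minimum share, so if a new message works few concurrent controls remain in the voice stage and voice versus standard SMS rests mainly on first-stage controls

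*Protocol article*

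**What the plan says.** The hypothesis in Objectives {7} is that "these messages will be associated with a higher attendance rate than the current standard SMS reminder". It covers both the new SMS and the voice message.

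Trial design {8} starts by "testing the two SMS reminder messages head-to-head with an initial 1:1 allocation ratio". Under Intervention description {11a} the comparator is "Arm 1 (Control): Standard SMS reminder messages". Arm 3 adds voice to the standard SMS and arm 4 adds voice to the new SMS. On timing: "We plan to introduce the voice message arms after 6 weeks".

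Once the first attendances are recorded, "the algorithm will begin adjusting the allocation ratio to favour the best-performing arms" (Sequence generation {16a, 16b, 16c}). Statistical methods {20a} gives the rule itself: "the proportion allocated to each arm for the next day will be updated to be proportional to the estimated probabilities". The text mentions no minimum share for control or for any other arm.

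Sample size {14} and Interim analyses {21b} apply two stopping rules: more than 95% probability that one arm is best, or more than 95% probability that the remaining arms differ by under 1%. They are checked daily, up to three months of active screening. Neither section exempts the two-arm stage.

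**The concern.** The algorithm is built to find the best arm, while the stated hypothesis is about beating the standard SMS. The two aims pull apart when a new message works. Control then loses its share, and part of that loss happens before two of the three experimental arms exist. Arm 3 against arm 1 is the contrast that isolates voice when added to the standard SMS, and in the voice stage it would have few randomised partners without voice.

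What is at stake is the quality of the voice comparison. If it leans on children randomised in the first six weeks, any change over time in attendance, or in the schools being screened, is mixed with the voice effect. The article does not state the order in which schools are screened, so the size of such drift is unknown.

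**Working it through.** **1. The one checkable figure.** Statistical methods {20a} gives a prior centred at 0.5 with a 90% credible interval of 0.44 to 0.56. Beta(100,100) has 5% and 95% quantiles of 0.442 and 0.558, which match. Beta(100000,100000) gives 0.498 to 0.502, which does not. Beta(100,100) is used below.

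**2. Inputs from the article.** Sample size {14}: "we expect approximately 160 of these children to be identified as requiring referral for further assessment and treatment", taken as 160 randomised a day. Control attendance is about 50% (Background {6a}). Appointments are about one week after referral (Outcomes {12}), taken as a lag of 5 working days. Two arms run for six weeks (30 working days), then four arms to three months (day 65), leaving 35 days and 35 × 160 = 5,600 children.

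**3. Assumptions.** Effect sizes; new arms enter at the prior; where the rules are live, they are not applied in the first 5 days after voice opens.

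**4. A bound before voice opens.** If the 95% rule is live and the two-arm trial is still running, the new SMS has at most 95% probability of being best. Control's share is then at least 5%, or 0.05 × 160 = 8 children a day.

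**5. Simulation of the stated rule** (150 to 1,000 trials per scenario). Control counts are medians for the voice stage.

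| Attendance %, arms 1/2/3/4 | Stops before voice opens, rules live | Controls, rules live, trials reaching voice | Controls, rules suspended until voice opens |
|---|---|---|---|
| 50/50/50/50 | 30% | 868 | 821 |
| 50/52/52/54 | 51% | 195 | 82 |
| 50/50/55/55 | 22% | 172 | 169 |
| 50/52/55/57 | 51% | 124 | 48 |
| 50/53/53/56 | 70% | 112 to 147 | 44 |
| 50/55/53/58 | 94 to 97% | 59 to 96 | 7 |
| 50/55/55/60 | 94% | 66 | 5 |

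Ranges show the spread over repeat simulations. With the new SMS at 55%, few trials reach the voice stage (15 of 300 in one run), so those counts are rough.

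**6. Precision.** SE = √[p₁(1−p₁)/n₁ + p₃(1−p₃)/n₃]. The control term alone, √(0.25/n₁), gives:
- n₁ = 190: 3.6 points; n₁ = 60: 6.5 points. Adding arm 3's term gives about 4 to 7 points with the rules live.
- n₁ = 50: 7.1 points; n₁ = 7: 18.9 points; n₁ = 5: 22.4 points (rules suspended).

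With the rules live, two-sided 5% power for arm 3 against concurrent control is 0.26 at 50/50/55/55, 0.19 at 50/52/55/57 and 0.13 at 50/55/55/60. Pooling first-stage controls raises these to 0.87, 0.69 and 0.44, but those controls are non-concurrent.

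**7. With a 10% minimum for each open arm.** The guaranteed count is 0.10 × 160 × 35 = 560 per arm. At 50/55/53/58 the medians are about 566 controls and 729 in arm 3: √(0.25/566 + 0.2491/729) = 2.8 points. Over the scenarios with an effect, controls are about 560 to 670 and the SE is 2.2 to 2.8 points. For a true 3-point difference with SE 2.8, power is Φ(3/2.8 − 1.96) = Φ(−0.89), about 19%.

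**8. A minimum for control alone is not enough.** At 50/55/55/60 with the rules off, control minimums of 0, 10, 20 and 25% give power of 0.06, 0.31, 0.37 and 0.38. It levels off because arm 3 itself has only about 300 to 380 children while arm 4 leads.

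**The case against.** A reader might infer that the rule leaves almost no controls, so that voice cannot be compared with the standard SMS at all. The documents do not support that, for four reasons.

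- With the stopping rule live, as written, control cannot approach zero before voice opens (step 4). The very small counts need the rule to be suspended in the two-arm stage, and the article does not say that it is.
- The loss depends on something working. With no effects, control keeps roughly 800 to 900 children in the voice stage.
- The article describes no resetting of the posterior, so first-stage controls (median about 1,600 to 2,400 with the rules live) still count. A comparison exists, but it is partly non-concurrent.
- Moving children away from weaker arms is the purpose of Thompson sampling. The article gives finding the best arm as the aim, and says the staggered opening is meant to show how the algorithm handles new arms.

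All four stand and limit the claim. None supplies concurrent controls in the case that the trial hypothesises. The last does not settle the matter either, because Objectives {7} names the standard SMS as the comparator. The allocation flow diagram (Fig. 3) and Fig. 2 are not shown. If either sets a minimum share, the text should say so.

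**Conclusion.** The point holds in a conditional form. If any new message works and the trial reaches the voice stage, concurrent controls are too few for a useful randomised comparison of voice with the standard SMS, and the estimate would rest mainly on non-concurrent first-stage controls. The size depends on the stopping rule: roughly 60 to 190 concurrent controls with it live, and mostly about 5 to 50 with it suspended until voice opens and an effective new SMS (82 when the separate effects are only 2 points).

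A related gap may matter more. As written, the 95% rule runs from the start, and an effective new SMS would usually end the trial before voice is tested: in about 94% of trials at 55% attendance and about 70% at 53%.

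The figures rest on assumed effects and 160 randomised children a day. Statistical methods {20a} instead speaks of about 1,000 enrolling daily. At that number with the rules live, 100% of trials stop before voice with the new SMS at 55%, and 93% with it at 52%.

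**What to change.** 1. In Statistical methods {20a}, set a minimum daily share, for example 10%, for control and for each open arm while the voice arms run, and allocate the rest by the probability of being best.
2. State that voice-versus-control estimates use concurrently randomised children. Any analysis adding first-stage controls should be labelled as supportive.
3. State whether the 95% rule applies before the voice arms open. If it does, the trial may never test voice, and the minimum share then never operates.

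The cost is one line in the algorithm and slightly lower attendance in the voice stage. At 50/55/53/58 attendance falls from 56.1% to about 55.4%, and 0.007 × 5,600 is about 40 children. The change makes a concurrent estimate possible but does not promise adequate power for small effects. A balanced comparison of 50% with 55% at 80% power needs 1,565 per arm, well above the 560 that a 10% minimum guarantees.

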### Outcomes {12}

All children who are screened and found to need further assessment and treatment (e.g. refractive services) will be given an appointment, approximately 1 week later, at a specified field ‘triage and treatment’ clinic or at a specialist ophthalmic hospital clinic. The primary outcome is attendance at this pre-specified appointment on the appointment date (yes/no).

The Peek software retains a record of every referred child. When children attend for these appointments, they are checked in using Peek software. This automatically updates their attendance status. Attendance data will be automatically reviewed by an algorithm every 24 h. The great advantage of the Peek-based screening programme is that is a closed data system with complete, unified data records for every person screened, their referral status and their attendance status. No additional data collection activities are required.*Primary outcome*: attendance at clinic on invited date. This is a binary outcome measure (yes/no). We will compare mean outcome rates between arms.*Secondary outcome*: days elapsed between appointment date and attendance. This is because children may miss their appointed day but attend at a later date. We will compare mean number of days elapsed between each arm.*Subgroup analyses*: attendance by age, sex, urban/rural residence, distance to clinic, ethnicity, guardianship, religion, language, household composition, migrant status, parental occupation, housing, assets and income.

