### Recruitment {15}

Community sensitisation is being led by the Ministry of Health and Ministry of Education. This includes TV and radio coverage explaining the Pono Yame screening programme. Our field coordinator will visit each region and work with schools to ensure that they are set up to enrol as many children as possible. Every referred child’s data will be included in the primary analysis. Subgroup analyses will only be permitted for children whose parents have consented for their sociodemographic data to be used for research purposes. This is a separate consenting process led by Peek.

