#### Interim analyses {21b}

This is an automated adaptive trial. Our algorithm will review the attendance data every 24 h and perform statistical testing. Two stopping rules will be applied during these daily interim analyses:There is a >95% probability that one arm is best.There is a >95% probability that the difference between the arms remaining in the study is <1%.

If neither of these rules have been satisfied, then the trial (i.e. enrolment) will continue until three months of active screening have elapsed. The Bayesian algorithm will adjust the allocation ratio based on the performance of each arm with respect to the updated posterior probability that each is associated with attendance (Fig. 3).

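### Cumulative attendance rates per arm, with no calendar-time term, can turn a shift in attendance into an apparent voice-message effect, because the voice arms start six weeks late

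*Protocol article*

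**What the plan says.** Statistical methods {20a} sets out the engine of the trial: "Every 24 h, the probability of each arm being the best arm overall will be estimated". If the trial continues, "the proportion allocated to each arm for the next day will be updated to be proportional to the estimated probabilities". On tools it says "We will conduct all analyses using the runif and rbeta functions in R". That means one beta posterior per arm, built from that arm's accumulated successes and failures.

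Interim analyses {21b} stops on the same posterior: "There is a >95% probability that one arm is best". Outcomes {12} says of the primary outcome: "We will compare mean outcome rates between arms".

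Trial design {8} starts with the two SMS arms at 1:1, "then introduce the voice messages after a period of six weeks". Intervention description {11a} repeats this: "We plan to introduce the voice message arms after 6 weeks".

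No section restricts a comparison to children randomised over the same dates, or puts calendar time, school or region into the arm comparison. The only regression described is the exploratory sociodemographic model in {20b}.

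**The concern.** Randomisation balances the arms within a day. It does not balance cumulative arm totals when the allocation ratio differs between days, and still less when two of the four arms have no data from the first six weeks. If underlying attendance differs between the early and late parts of the trial, arms 1 and 2 average over both parts while arms 3 and 4 reflect only the later one. The gap then looks like a message effect.

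The same posterior steers allocation and stopping, so the error feeds back. Children are moved away from the SMS-only arms, which leaves fewer concurrent controls from which a later re-analysis could recover. Voice messaging is one of the two interventions named in Objectives {7}, so a main conclusion of the trial is exposed.

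**Working it through.** **Inputs from the protocol**
- Prior centred at 0.5 with 90% credible interval 0.44–0.56 ({20a})
- About 160 referrals a day ({14})
- Attendance about 50% ({6a})
- Appointment about one week after referral ({12})
- Three working months at most ({13}), with voice after six weeks ({8})
- 95% threshold checked daily ({21b})

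**Assumptions**
- 60 working days, voice from day 31, outcome known after 5 working days
- All four messages equally effective
- The drift sizes shown

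**Step 1: the stated prior.** Beta(100,100) has 5th and 95th percentiles 0.442 and 0.558, which reproduces the stated interval. The printed parameter, Beta(100,000), looks like a misprint and does not affect this point.

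**Step 2: closed form, equal allocation.**
- Each SMS-only arm has 30 × 160 / 2 = 2,400 children before voice entry and 30 × 160 / 4 = 1,200 after. Each voice arm has 1,200, all after.
- For a step change d at voice entry, the false voice-minus-SMS difference is d × (share of the SMS arm's data from before entry) = d × 2,400 / 3,600 = 0.667d.
- For d = +5: SMS = (2,400 × 0.50 + 1,200 × 0.55) / 3,600 = 51.7%, voice = 55.0%, difference +3.3 points.
- For d = +2, +10 and −5 the differences are +1.3, +6.7 and −3.3 points.
- Posterior means at d = +5: SMS (1,860 + 100) / (3,600 + 200) = 0.516, voice (660 + 100) / (1,200 + 200) = 0.543. With posterior SDs of about 0.008 and 0.013, the probability that one voice arm beats one SMS arm is about 0.96, although the messages are identical.

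**Step 3: adaptive allocation.** Once voice looks better, the SMS-only arms receive fewer late children, so the early share in the formula rises above two thirds. In simulations of the stated algorithm, a +5 step gives a mean pooled difference of 4.5 to 4.6 points (4.5 / 5 = 90% of the step). With stopping from voice entry, stratifying the same data by day gives about +0.1 to +0.2, no more than with no drift (+0.1). A −5 step gives about −3.2.

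**Step 4: the protocol's own rule.** Probability that a voice arm is falsely declared best (400 to 800 simulated trials per scenario for most runs):

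| Drift | False voice winner |
|---|---|
| None | 1.2–2.5% |
| +2 step | 11% |
| +3 step | 15% (rule active from day 1), 19% (from voice entry) |
| +5 step | 17–35% across runs; e.g. 22.6% from day 1, 34.5% from voice entry |
| Linear +5 over the trial | 16% (from voice entry) |
| −5 step | 0% |

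**Step 5: daily reallocation alone.** With only the two SMS arms, equal in effect and with stopping from day 1, a linear 10-point rise moves the false-winner rate from 36% to 81%, and a 10-point fall moves it to 20%. So drift enters even without staggered entry.

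**Step 6: the remedy.** With day fixed effects and the rule active from voice entry, false voice winners are 2.6% with no drift, 2.0% at +5, 2.2% with a linear 10-point rise and 1.6% at −5. With the rule active from day 1, the +5 figure is 1.2%.

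**The case against.** The best defence is that no drift is documented. Recruitment {15} says only "Our field coordinator will visit each region and work with schools"; it gives no order of regions and no expected change in attendance. That stands: drift is plausible in a new national programme, but its size and direction are assumed here.

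Second, the sentence on R functions cannot literally cover all analyses, because {20b} uses logistic regression, and a final model may sit in an analysis plan that is not shown. This stands in part. An unadjusted final comparison is an inference from {12} and {20a}. The daily posterior behind allocation and stopping is fixed in the text.

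Third, staggered entry and shifting allocation are deliberate. That justifies the design, not comparing non-concurrent children.

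Four stronger readings are tempting and not supported:
- **Any drift biases the result.** Drift during the initial 1:1 period does not bias the two-arm comparison, and a 2-point shift has a modest effect.
- **A false voice win is near certain.** Both voice arms together against both SMS-only arms, ignoring stopping, do pass 95% in 98–99.8% of simulated trials at +5. The protocol's rule asks for one best arm, and two equal voice arms split that probability.
- **The control arm will be starved after voice entry, so a minimum allocation is essential.** If the new SMS truly adds 5 points, about 94% of simulated trials stop before voice entry.
- **The 36% two-arm false-winner rate without drift belongs to this point.** It comes from daily looks at a 95% threshold, and time adjustment does not remove it.

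**Conclusion.** The point holds for the daily posterior as written and, by inference, for the stated comparison of mean rates. Following the plan can give a wrong answer about voice messages if attendance shifts after the initial 1:1 period. Under the assumed +5-point step at voice entry, the false difference is about 3.3 points (equal allocation) to 4.5 points (adaptive). The chance of a false voice winner rises from about 1–3% to 17–35%; for +3 it is 15–19%. A fall of 5 points gives about −3.3 points and no voice winners, so a real benefit could be hidden. These sizes rest on the assumed drift, the 60-day calendar and the 5-day outcome delay. The structural imbalance between early and late data does not. It should be settled before enrolment, which had not begun at protocol version 1.2, because allocation and stopping cannot be redone afterwards.

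**What to change.** State in {20a} and {21b}, for both the daily algorithm and the final analysis, that arms are compared only among concurrently randomised children. Either of these would do:
- a Bayesian logistic model with arm plus day or week of referral, and location where available, with the regularising prior restated for the arm effects; or
- a risk difference stratified by day or week.

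Compare the voice arms with arms 1 and 2 only from voice entry onward, and amend {12} to match.

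The data burden is small: the software records the attendance date and the time since referral ({17a}), and location is collected ({27}), though school as such is not listed there. The cost is a somewhat larger model than independent beta draws, and less precision for voice comparisons when few children are concurrently allocated to SMS only.

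A minimum allocation per arm would protect that precision but is optional, since it works against the stated aim of favouring better-performing arms. False stopping from daily looks needs its own remedy.
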